## **Procedures**

All testing will take place in the NICU and Intermediate Nursery at C&W. As in our previous studies, five minutes before, during and five minutes after the tn-ECHO procedure, a close up image of each infant's face and upper extremities are videotaped. The digital, color camera is set up using a tripod. Using a foot pedal attached to the camera, recordings are synchronized to mark events. These tapes will be used to provide blinded behavioral coding of our primary outcome measure in conjunction with our bedside scoring described below.

For all groups, each infant will remain in his/her incubator/cot, positioned with rolls around the body to promote a flexed position. Every attempt will be made to have the procedure scheduled one hour post feed, if the infant is feeding. After a 20 minute rest period, five minutes before the contact of the physician to conduct the examination, an attending physician who is not conducting the tn-ECHO will assess the infant's baseline stress levels over a 30 second period using the Behavioral Indicators of Infant Pain (BIIP). BIIP score will then be measured 2 min after first administration of the solution (at time of starting of the tn-ECHO), then halfway through the assessment (as defined per echocardiographical images obtained, after completion of the right ventricular long axis view with RVO), and finally immediately after the last contact of the physician.

With respect to the glucose/water administration, two minutes before the first contact by the physician performing the tn-ECHO, each infant will be given either 0.5ml of 25% glucose (26-31 weeks gestational age group) or 1.0 ml of 25% glucose (32-42 weeks gestational age group). The solution will be applied to the anterior portion of the tongue followed by insertion of a soother. The soother will be held in the infant's mouth to ensure that continuous contact is maintained throughout the testing period. During the course of the assessment (estimated about 20 min), this application can be repeated if necessary (if the infant's movements interfere with the quality of picture obtained) to a maximum of four times, adding up to max 2ml of 25% glucose in the 27-31 weeks gestational age group or 4ml of 25% glucose in the 32-40 weeks gestational age group. During each tn-ECHO, infants have additional handling only if it is required to maintain physiological stability. Pharmaceutical interventions are an exclusion criterion for the study.

For the infants randomized to receive facilitated tucking throughout the procedure, the bedside nurse will provide gentle, firm containment of the extremities. The facilitated tucking will commence immediately after the baseline BIIP score is taken, but before the glucose/water is administered. The NICU nurses have all been trained to use this technique for other procedures and so are very familiar with the technique. The nurse will continue to hold the infants until the tn-ECHO is complete.

Scans will be done by neonatologists or neonatologists in training (fellows) trained in tn-Echo. It will always comprise the following standardized assessment:

- Left ventricular performance (Contraction in 4- and 5-chamber views, long and short axis view, VTI, LVO, fractional shortening, IVRT, E:A ratio)
- Right ventricular performance (Contraction 4- and 5-chamber views, long and short axis view with RVO, septum deviation)
- Shunts (PDA: Presence, flow pattern, size and peak velocity; PFO/ASD/VSD)
- End-organ blood flow: Celiac artery Doppler, MCA Doppler

Following each procedure, infants will be monitored for a 5 minute recovery period. One minute following the examination, the infant's stress will be measured again using the same standardized scoring system (BIIP; see below).

Data will be collected using a data collection sheet. Timing of tn-ECHO will be recorded as initiation of echo defined as application of the probe to the infant's chest. End time of echo will be recorded when the probe is removed from infant's chest. Time and amount of solution as well as application of soother and facilitated tucking, BIIP scores and adverse events will be also recorded on the data collection sheet. Upon completion of study, the research nurse will complete an environmental score, documenting the maximum environmental noise, to provide information regarding outside factors that could influence the infants' stress level during the procedure (i.e. light, noise, etc.). If desired by the family, we will provide them with a de-identified non-diagnostic image of their infant's heart to keep.

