## **Inclusion Criteria**

Infants born between 26-42 weeks of gestational age admitted to the Neonatal Intensive Care Unit and Intermediate Nursery at Children's and Women's Health Centre of British Columbia (C&W) who are stable enough to have a tn-ECHO. To avoid bias in completing time of the tn-ECHO we have excluded purely educational studies.

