## **Methods**

Parents will be asked for written informed consent prior to randomization. It is not standard of practice to obtain parental consent for procedures like echocardiography that are clinically indicated; therefore, the consent will be purely for research purposes.

One hundred and four infants will be randomized to one of four intervention groups (Grp 1: glucose + soother; Grp 2 glucose + soother + facilitated tucking; Grp 3: water + soother; Grp 4: water + soother+facilitated tucking) which will take place during a single tn-ECHO examination, at the discession and after consultation with the medical team.

Randomization to each group will be determined by generating randomly permuted sequential blocks of four and six allocation numbers. The Clinical Services Research Unit will initiate the randomization process and provide the information regarding group allocation that will guide the intervention. Access to the randomization list will be through a web-based system that will enable online interactive checking of the inclusion/exclusion criteria before authorizing random allocation. This system is very reliable with 24-hour on-line support; as part of the data management services, a person will be available by phone during working hours at C&W to provide back-up for the system for unanticipated events. Randomization and preparation of the solutions will then be done by the pharmacist on site who will provide the solutions in unmarked syringes containing 5ml of either water or 25% glucose.

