## **Statistical Analyses**

Demographic and medical information about the infants will be compared between groups to ensure balance. Then, the primary outcome for analysis will be defined as the between group difference between average BIIP scores in the pre and during echocardiography observations. Mean change scores will be calculated and a 2 Group (Intervention) by Phase (Baseline, Echo) analysis of variance will be used to determine main effects. The confidence interval for the difference in treatment effects will be of primary interest. Any differences in baseline BIIP scores or medical/demographic variables found would be included as co-variables in the analysis. Differences between tn-ECHO times between groups, in the total number of times solutions are administered for each group, and in the overall quality ratings of the tn-ECHOs will be compared using paired t tests.

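### Scans may be done by neonatologists or fellows, but the protocol does not list operator as recorded data or name the operator before allocation, and it compares the three scan-related secondary outcomes without adjusting for operator; the main cost is precision.

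*Protocol*

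**What the plan says.** - **Who scans.** Protocol, Procedures: "Scans will be done by neonatologists or neonatologists in training (fellows) trained in tn-Echo". The views to be obtained are standardized. No section says how the operator for an infant is chosen, or when.
- **Which scans count.** Protocol, Inclusion Criteria: "To avoid bias in completing time of the tn-ECHO we have excluded purely educational studies".
- **Allocation.** Protocol, Methods: "One hundred and four infants will be randomized to one of four intervention groups", and "Randomization to each group will be determined by generating randomly permuted sequential blocks of four and six allocation numbers". No stratification factor is stated.
- **Masking.** The pharmacist is the one "who will provide the solutions in unmarked syringes containing 5ml of either water or 25% glucose" (Methods). Tucking is done by hand by the bedside nurse. It starts after the baseline BIIP score, before the solution is given, and lasts until the scan ends (Procedures).
- **Repeat applications.** Procedures: "this application can be repeated if necessary (if the infant's movements interfere with the quality of picture obtained) to a maximum of four times". Who makes that judgement is not stated.
- **Data listed.** Neither the data collection sheet described in Procedures nor the list under Other Data Collected mentions operator identity or grade. The second list is open-ended, but it concerns clinical information about the infant.
- **Analysis.** For scan time, number of applications and image quality, Statistical Analyses ends with the differences "in the overall quality ratings of the tn-ECHOs will be compared using paired t tests". No covariate is named for them. The covariate sentence, "Any differences in baseline BIIP scores or medical/demographic variables found would be included as co-variables in the analysis", comes directly after the BIIP analysis of variance.

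**The concern.** All three secondary outcomes pass partly through the operator. Scan time runs from probe on to probe off. Image quality is the quality of what the operator acquired. Repeat applications depend on whether movement is judged to spoil the picture. If fellows and neonatologists differ on these, the difference stays in the error term of an unadjusted test and widens every interval.

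This matters beyond the analysis plan. A later analysis cannot adjust for an operator who was never recorded, and naming the operator before allocation can only be arranged in the conduct of the trial. Scan time and image quality also carry the resource and quality benefits that the Protocol claims under Significance/Impact.

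**Working it through.** **The plan's own figure.** The only power statement is for BIIP: 25 per group, 80% power, 2 points. No SD or alpha is given. At two-sided 5% the implied SD is 2/[(1.960 + 0.842) × √(2/25)] = 2.52, so 25 is plausible but cannot be confirmed. No sample size is given for the outcomes discussed here, so there is no stated figure to reproduce for them.

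**Inputs.** From the Protocol: 100 infants in the power statement, so 50 against 50 on each factorial margin; 104 randomized, so 26 per arm and 52 per margin. Assumed, because the Protocol is silent: fellow share p of 0.5 or 0.3; a gap g between grades of 0.25 to 1.5 within-grade SD; equal SD within grades; two-sided 5%.

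**Step 1: precision.** With grade left out, variance is inflated by V = 1 + p(1 − p)g². For p = 0.5 and g = 1, V = 1 + 0.25 × 1 = 1.25. Take a difference that has 80% power when grade is adjusted for. Power without adjustment is Φ(2.802/√V − 1.960). For V = 1.25 this is Φ(2.506 − 1.960) = 70.7%. Infants needed per side to regain 80% are 50 × V, rounded up.

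| g (SD) | V, p = 0.5 | Power | Per side instead of 50 | V, p = 0.3 | Power |
|---|---|---|---|---|---|
| 0.25 | 1.016 | 79.4% | 51 | 1.013 | 79.5% |
| 0.5 | 1.063 | 77.6% | 54 | 1.053 | 78.0% |
| 1.0 | 1.250 | 70.7% | 63 | 1.210 | 72.1% |
| 1.5 | 1.563 | 61.1% | 79 | 1.473 | 63.6% |

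The power loss is the same for single arms, because the reference difference is scaled to the sample size.

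**Step 2: chance imbalance.** With p = 0.5, the SD of the difference in fellow share is √(2 × 0.25/n). For n = 52 it is 0.098 (95% limits ±19 percentage points); for n = 26 it is 0.139 (±27 points). These shifts are part of the sampling error that an unadjusted standard error already contains. They are the same cost as Step 1 seen another way, not an addition to it.

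**Step 3: bias, if the choice of operator followed the arm.** This is a what-if calculation. Suppose the fellow share differs by q = 0.2 between tucking and no tucking, at 50 against 50. Bias is q × g, and the standardized shift is qg/[√V × √(2/50)].
- g = 1.0: bias 0.2 SD; shift 0.2/(1.118 × 0.2) = 0.894; error rate Φ(0.894 − 1.96) + Φ(−0.894 − 1.96) = 14.5%.
- g = 0.5: bias 0.1 SD; shift 0.1/(1.031 × 0.2) = 0.485; error rate 7.7%.

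**The case against.** Four arguments on the other side have force.

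1. *The sections agree.* A reader might infer that Inclusion Criteria bars training scans and Procedures then lets trainees in. The documents do not support this. Only scans done purely for teaching are excluded, and the fellows in question are trained in the technique. A clinically indicated scan by a trained fellow satisfies both sections.
2. *Randomization deals with bias.* A reader might infer that a chance excess of fellows in one arm biases the result. It does not: operators balance in expectation, and chance imbalance is covered by the standard error. Systematic bias would need the operator to be chosen, or to behave differently, with knowledge of the arm. Nothing in the Protocol says that this happens. It is implausible for masked glucose against water. For tucking it is possible, since the arm is visible before the probe is applied, but it remains conjecture.
3. *Adjustment is not ruled out.* A reader might take the covariate sentence as forbidding operator as a covariate. It most naturally belongs to the BIIP analysis, and an analysis plan that is not shown could add covariates. What remains is that the Protocol itself names unadjusted tests for these outcomes, and does not list the variable that adjustment would need.
4. *The operator is only one influence.* Infant movement is the intended driver, the views are standardized, and two raters blind to group score the images. These reduce the operator effect. Blinded rating prevents biased scoring, but it cannot remove real differences in the images acquired.

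It is also fair that not stratifying by operator is a normal choice in a trial of this size.

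**Conclusion.** The point holds as a matter of efficiency for secondary outcomes. The size rests wholly on an assumed operator mix and gap. At a gap of 0.5 SD or less the loss is small (80% to 78% power); at 1.0 to 1.5 SD with half the scans by fellows it is material (71% to 61%). Bias is limited to a possible route for tucking against no tucking, and the error rates in Step 3 illustrate that route without showing that it operates. The primary BIIP comparison is not called into question. The change is worth considering because it is cheap, not because the plan is invalid without it.

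**What to change.** - Add operator code and grade (neonatologist or fellow) to the existing web form, completed before allocation is released. Record on the data sheet who actually scanned, so that any change of operator can be seen.
- Replace the unadjusted t tests for scan time, number of applications and image quality with between-group models suited to each outcome's scale, with operator grade as a prespecified term.
- Stratifying allocation by operator grade is optional.

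The cost is one extra form field and one degree of freedom. The practical downside is that the operator must be named before allocation.

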## **Outcome Measures**

### *Primary Outcome Measure*

The primary outcome measure will include changes in BIIP scores across phases (Baseline, maximal score at first contact by physician, ½ through the tn-ECHO, Recovery) of the study. The Behavioral Indicators of Infant Pain (BIIP) is a reliable and valid scale we developed for assessing acute procedural pain in preterm infants, although it can also be used for measuring stress.

The BIIP combines into a single scale changes in sleep/wake states, five facial actions and two hand actions. The scoring sheet is appended. Scores range between 0-9, with scores 0-2 indicating mild or no pain/stress, 3-6 indicating moderate pain/stress and scores 7-9 indicating more severe pain/stress. In response to heel lance, under conditions where no intervention is provided, mean scores on the BIIP were  $5.3 \pm 2.6$  points. For less intrusive, but stressful procedures, such as diaper change, mean BIIP scores were  $3.1 \pm 0.5$ . To ensure reliability for

BIIP coding, physicians will be trained by [name] to achieve inter-rater reliability on the scale to above 0.85 (kappa). After the first 20 sessions, inter-rater reliability will be checked using the Bland and Altman approach which analyzes the differences in scores between two coders over the pair-wise mean of the two coders.

From the bedside videotapes, using the Noldus Observer system^16, one, 30-second block will be coded in real-time across four procedure phases:

|            |                                                                     |
|------------|---------------------------------------------------------------------|
| Baseline   | [T0] = 30 seconds, 5 minutes before first contact by the physician, |
| Time 1     | [T1] = 30 seconds beginning 2 minutes after first solution given,   |
| Time 2     | [T2] = 30 seconds after 4 and 5 chamber views finished              |
| Recovery 2 | [T3] = 30 seconds after the last contact by the physician           |

As we have done in other studies, study phases will be randomized for viewing. Two graduate student video coders will be trained to achieve inter-rater reliability on the BIIP to above 0.85 (kappa) by our research nurse who has extensive experience scoring the BIIP. To ensure inter-rater reliability is maintained, during the trial, an additional 20% of the video segments selected randomly will be scored by the research nurse and the video coders. Inter-rater reliability will be assessed using the intra-class correlation (ICC), and graphically using the Bland and Altman approach by plotting the pair wise differences in scores between two coders against subject specific means over the two coders.

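### If first contact runs late, the contact-anchored video baseline slides into the tucking period in Groups 2 and 4 only

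*Protocol*

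**What the plan says.** Two parts of the protocol fix the timing.

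- **Procedures, bedside baseline.** After the rest period, and "five minutes before the contact of the physician to conduct the examination", a physician who is not scanning "will assess the infant's baseline stress levels over a 30 second period" with the BIIP.
- **Procedures, tucking.** "The facilitated tucking will commence immediately after the baseline BIIP score is taken, but before the glucose/water is administered". Methods assigns tucking to Groups 2 and 4 only.
- **Procedures, solution.** It is given "two minutes before the first contact by the physician performing the tn-ECHO", and the next bedside score is placed two minutes after it, which the text equates with the start of the scan.
- **Procedures, filming.** The infant is filmed "five minutes before, during and five minutes after the tn-ECHO procedure", with a foot pedal to mark events. Which events are marked is not stated.
- **Primary Outcome Measure, video table.** T0 is "30 seconds, 5 minutes before first contact by the physician"; T1 is "30 seconds beginning 2 minutes after first solution given".

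The tapes supply blinded coding of the primary outcome, alongside the bedside scores. Statistical Analyses compares BIIP before and during the scan, and would add any baseline BIIP difference between groups as a covariate.

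**The concern.** The bedside baseline is taken prospectively, against a planned contact time, and tucking follows it. The video baseline is located afterwards, by counting back from contact. These are the same 30 seconds only if contact happens exactly when planned. The protocol gives no tolerance and no rule for which event governs when it does not.

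Late contact moves the video baseline in one direction, into a period when two of the four arms are already receiving a randomized intervention. T0 is the only pre-scan video score, so every video change score depends on it. A mechanical effect is plausible: tucking holds the limbs, and the BIIP scores two hand actions. If tucking calms the infant, the baseline in Groups 2 and 4 is lowered and the benefit of tucking is understated. If being handled rouses the infant, the error runs the other way. A baseline difference created in this way could also trigger the covariate adjustment, which would then adjust for part of the treatment effect.

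T1 has a related but lesser problem. The primary outcome names this phase by first physician contact, while the video block is timed from the solution.

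**Working it through.** **Inputs**, in seconds, with planned first contact = 0 and D = seconds by which actual contact is late:

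- Bedside baseline: starts at −300 and lasts 30, so [−300, −270] (Procedures).
- Tucking, Groups 2 and 4: from −270 (Procedures; Methods).
- Solution: −120 (Procedures).
- Filming: from −300 (Procedures).
- Video T0: 30 s starting 300 s before actual contact, so [D − 300, D − 270] (Primary Outcome Measure).
- Video T1: solution + 120, so [0, 30] (Primary Outcome Measure).

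**On schedule (D = 0).** T0 = [−300, −270] and tucking starts at −270, so the overlap is 0 s. T1 starts at −120 + 120 = 0, which is contact. The protocol's own timing is reproduced, and the anchors agree.

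**Late contact, T0.** Overlap with tucking = (D − 270) − max(D − 300, −270) = min(D, 30).

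| D (s) | Video T0 | T0 inside tucking, Groups 2 and 4 |
|---|---|---|
| 0 | −300 to −270 | 0 s |
| 15 | −285 to −255 | 15 s |
| 30 | −270 to −240 | 30 s (all) |
| 60 | −240 to −210 | 30 s (all) |

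The overlap is zero in Groups 1 and 3 because they have no tucking. The bedside baseline stays at [−300, −270] whatever D is.

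**Early contact.** At D = −30, T0 = [−330, −300]. If filming was timed to planned contact, the whole block precedes the tape.

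**Late contact, T1.** If the delay arises after the solution has been given, T1 stays at [0, 30] and min(D, 30) s of it precedes contact, in all four groups. If the solution is held back to D − 120, T1 = [D, D + 30] and none of it precedes contact. The T0 overlap is the same in both cases.

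**Sensitivity to where T0 sits.** If the video block ended at −300 while the bedside score started there, T0 = [D − 330, D − 300]. The overlap is then 0 s at D = 30 and 30 s at D = 60. The filming window favours a block that starts at −300, since one that ended there would not be on tape.

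**Size of the bias.** Let p be the share of tucked infants whose T0 lies wholly inside tucking, and δ the shift in BIIP from being tucked at rest. The mean baseline in those arms moves by p × δ, and the tucking contrast in change scores moves by the same amount with opposite sign. The protocol gives neither p nor δ. For illustration only, with δ = 1 point in size, p = 0.1, 0.3 and 0.5 give 0.1, 0.3 and 0.5 points, against an anticipated difference of 2 points.

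**After the fix.** With T0 tied to a mark made before tucking, the overlap is 0 s at every D.

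**The case against.** The strongest reply is that nothing here is contradictory: on the written schedule the blocks line up, and the fault appears only when timing slips. That stands. This is a fragile definition, and the protocol gives no evidence on how often contact is late.

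It is also fair to say that staff could place T0 correctly. Pedal marks exist, times of solution and tucking go on the data sheet, and a nurse's hands would probably be visible on a film of the face and arms. But no rule tells the coder to use any of these, and the only rule written counts back from contact.

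Four stronger readings are tempting and not supported:

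- **That the trial's baseline as such becomes a post-intervention score.** Only the video baseline can. The bedside score precedes tucking by definition.
- **That any 30-second late start puts T1 before contact.** This requires the delay to arise after the solution has been given. Procedures ties the solution to contact, so a delay known earlier leaves T1 intact.
- **That T0 may fall after the solution in every arm.** This needs contact three minutes late, hence at least five minutes after the solution, a clear departure from the two minutes planned.
- **That a pre-contact T1 dilutes every contrast by a known amount.** Supposing no treatment difference at T1 sits badly with supposing that tucking alone shifts the score by 1 point. With 30% late starts and a 2-point effect averaged over T1 and T2, the first supposition loses 0.3 × ½ × 2 = 0.3 points. If a 1-point calming effect persists, the tucking contrast loses 0.3 × ½ × (2 − 1) = 0.15. Neither is a result.

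**Conclusion.** The point holds for the video baseline. Its definition has no margin against late contact, and the resulting error is differential: min(D, 30) seconds of T0 inside tucking, in Groups 2 and 4 only, complete at 30 seconds. This rests on three assumptions: contact slips after the baseline has been scored and tucking begun; the coder counts from actual contact; and T0 starts, not ends, five minutes before it. The bias would fall on the tucking effect in video change scores, towards the null if tucking calms and away from it if handling rouses. Its size cannot be estimated from the protocol.

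For T1 the conclusion is narrower. The solution-based anchor and the first-contact label describe the same moment only if contact comes two minutes after the solution, and the protocol does not say which prevails otherwise. Timing T1 from the solution is not wrong in itself, since it keeps the solution-to-score interval constant.

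**What to change.** - **T0.** In the video table, define T0 as the same 30 seconds as the bedside baseline score, ending at a foot-pedal mark made before tucking, solution or soother in every arm.
- **Filming.** Begin a few minutes earlier, within the existing rest period, so that this block is on tape even if contact comes early.
- **T1.** Record the solution-to-contact interval for each infant and state which event governs T1 when the interval is not two minutes. Re-anchoring T1 to probe contact is optional. It would match the phase label better but give up a fixed solution-to-score interval.

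The cost is a few words in Procedures and in the video table, one extra pedal mark and a little more tape. No treatment timing changes. The change should be made before recording starts, because a baseline that was never filmed cannot be recovered.
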